#### Primary outcome analysis: adjusted analysis

In the event that there is a baseline imbalance between the treatment groups in a baseline covariate due to chance, we will perform an adjusted (sensitivity) analysis (see below). This is particularly important if CHX has a better outcome than NATA, as the adjusted treatment effects may account for this observed imbalance while the unadjusted analyses may not. Sensitivity analyses will allow us to show that any observed positive treatment effect is not solely explained by imbalances at baseline in any of the covariates.

#### Secondary analyses of the primary outcome

##### Per-protocol analysis

Repeat analysis of the primary outcome will be done as per the protocol, based on what the participants actually took. The per-protocol population will include all the individuals included in the primary ITT analysis, excluding individuals who showed poor compliance with the medications (defined as taking less than 50% through self-reporting or bottle weighing, whichever is the lower); individuals where there have been major protocol deviations; and non-fungal or mixed corneal infections (should these patients happened to have been randomised). All analyses that are performed as ITT will be repeated as per protocol and labelled as such.

##### Mixed infections

Secondary analysis of the primary outcome (by ITT) will include mixed infections and will be carried out in the same way as in primary analysis of the primary outcome above.

##### Sensitivity analyses

For the primary analysis those individuals with missing outcome data (ie, lost to follow-up) will be excluded. Sensitivity analyses will be performed by imputing a range of scenarios to demonstrate a range of potential results, where there is missing outcome data. In the case of substantial missing data in the trial, the primary analysis will be carried out as previously stated excluding missing observations. This, however, assumes data are missing completely at random. As a sensitivity analysis, we will then apply a multiple imputation approach to the missing data, if we consider the data are randomly missing conditional on other observed covariates.

In the case that there is a systematic (ie, non-random) reason for a difference in the follow-up rates between the two groups, we will explore models in which these missing outcome data are assumed to be non-random, that is, dependent on the outcome being regressed, BSCVA or treatment group.

We will also perform sensitivity analyses on patients whose vision is CF or worse, those patients who have undergone a TPK or those with corneal perforation, to see if there is any change in the effect size or conclusions drawn.

##### Analysis of other potential determinants for success

Logistic regression random-effects models will be used to analyse potential factors that may be associated with a poor primary outcome, BSCVA at 3 months, defined as >1.0 logMAR. Individual baseline characteristics will be used separately as an exposure variable with BSCVA at 3 months as the outcome, with the model adjusted for trial arm. A multivariate model will be built using parameters with a p<0.2 in the log likelihood ratio test. Variables will be removed one by one, by omitting the variable with the largest p value each time, until all predictors in the model have a p<0.05.

#### Secondary outcome analysis

The secondary outcomes outlined above and detailed in table 4 will be analysed by arm. Additional adjustment for factors imbalanced between arms at baseline will be introduced as appropriate. Continuous outcomes will be analysed using linear regression. Binary and ordinal outcomes will analysed using logistic regression. Details of these are given in table 4.

**Table 4 T4:** Secondary outcome measures that will be investigated as part of the trial, together with analysis details

Secondary outcome measure	Details
Three-week BSCVA	We will analyse the secondary outcome of 3 weeks BSCVA in logMAR in the same manner as the primary analysis of the primary outcome described above. The 3 weeks BSCVA will include values taken between 18 days and 5 weeks, with the value closest to 3 weeks used.
Presenting VA by Peek	We will analyse the presenting VA by Peek Acuity with and without pinhole at 3 months as a secondary outcome. This will be of interest if we are unable to get reliable BSCVA measurements at 3 months (ie, if patients fail to attend and we need to attend their houses for visual acuity testing). This will be performed in the same way as the primary analysis of the primary outcome. We will also perform a sensitivity analysis including those lost to follow-up, by using the most recent observation of this variable.
Scar/infiltrate size at 1 week, 3 weeks and 3 months by slit lamp examination	The geometric mean of the two principle axes in mm of the scar or infiltrate at 1 week, 3 weeks and 3 months will be used as a secondary outcome variable. The slit-lamp scar size will be compared at each of these time points between treatment arm in the same manner as described above. This will be by linear regression, with treatment arm and baseline infiltrate/scar size as pre-specified covariates. This controls for the baseline infiltrate/scar size.
Time to full epithelial healing (slit lamp examination by ophthalmic clinician)	Time of re-epithelialisation will be defined as the midpoint between the last review where an epithelial defect (ED) was present and the subsequent review where there was no ED. An area of fluorescein staining of less than 0.5 mm will be considered as a resolved ED due to the difficulty in differentiating a smaller defect from a small amount of fluorescein pooling observed in a healed defect.
	Analysis of time to healing will use Cox proportional hazards regression with treatment group as the primary predictor and with predictors of baseline ED size (using the geometric mean in mm as outlined above). Survival curves will be plotted using Kaplan-Meier analysis for both treatment arms up to the final visit at 3 months. The proportional hazards assumption will be checked by stratifying on quartiles of the baseline ED size and if the assumption does not hold, the stratified results will be the ones reported. Additionally, treatment failure (defined as persisting epithelial defect greater than 0.5 mm at the 3 month review) will be compared between treatment groups using Fisher’s exact test.
Rate of healing	We will assess how quickly the area of ulceration reduces over time. The rate will be calculated between the 1-week, 3-week and 3-month review by taking the difference in ED size between the two time points, in mm, and diving by the number of days to give a rate of mm/day. Analysis will be performed using Cox regression.
Microbiological cure	Patients who have a persisting corneal ulcer (as defined by the presence of an ED) at day 7 will undergo a repeat corneal scrape and microbiological investigations. Microbiological cure at 7 days will be defined as the absence of any micro-organisms as no significant growth on culture. The number of patients with microbiological cure at day 7 will be compared between the two treatment arms using logistic regression with treatment group and organism (*Aspergillus* spp, *Fusarium* spp, or other) as covariates.
Ulcer depth at 1 week and 3 weeks (slit lamp examination by ophthalmic clinician)	The depth of ulcer in terms of percentage of healthy cornea will be compared at 1 week and 3 weeks between treatment arms, adjusting for baseline depth in the same manner with analysis performed by linear regression
Hypopyon height at 1 and 3 weeks, (slit lamp examination by ophthalmic clinician)	The hypopyon height in mm will be compared at 1 week and 3 weeks between treatment arms, adjusting for baseline hypopyon height in the same manner with analysis performed in the same way (linear regression)
Perforation and/or TPK and/or conjunctival advancement by 3 months (slit lamp examination by ophthalmic clinician)	The number of patients who undergo perforation and/or require TPK and/or have undergone conjunctival advancement by 3 months will be reported using CIs and descriptive statistics. The study is not powered to detect a difference in perforation rate or TPK between treatment groups; not reporting a significant difference may be wrongly interpreted as there being no difference between groups. We will therefore perform an exploratory analysis to compare TPK or perforation rates between treatment groups. This will be by logistic regression to compute an OR by arm.
Loss of eye	The number of patients who have their eye surgically removed (evisceration or enucleation) during the 3 months follow-up period will be reported using CIs and descriptive statistics in the same way as for TPK/perforation rate above, along with exploratory analysis using logistic regression to find risk factors for eye loss and OR for this by arm.
Ocular adverse effects, slit lamp examination by ophthalmic clinician	The proportion of patients with one or more adverse events will be compared using Fisher’s exact test. Additional analysis to compare the rate of adverse events during the 3 months follow-up will be by Poisson regression as this can take into account multiple instances within one participant.
QoL assessed using: EQ-5D, WHO/PBD-VF20, WHOQOL-BREF	QoL can be assessed quantitatively using different tools depending on what is of interest. For example, disease-related QoL can be assessed (eg, vision related QoL, VRQoL) or more general health-related issues irrespective of the disease can be investigated (health-related QoL, HRQoL).^40^
	We will use the WHO/PBD-VF20 (WHO/ Prevention of Blindness and Deafness—Visual Functioning 20-item questionnaire) VRQoL tool. This tool measures the impact of visual impairment in the person’s life including mental well-being, dependency and social functioning. These have been used in a number of other visual related studies to show a difference in QoL.^36 37^
	For HRQoL, we will use the EQ-5D questionnaire, EQ-Visual Analogue Scale and the WHOQOL-BREF. The EQ-5D is a standardised tool to measure health outcomes.^38^ The WHOQOL-BREF has good applicability in (LMIC as it was developed simultaneously from concept across 18 countries in Africa, Asia and Latin America. It measures four domains of health: Physical Health, Psychological Health, Social Relationships, and Environment. Details of this scoring are given in table 2.^39^
	Analysis will be by comparing the scores obtained for each QoL assessment for the two treatment arms to estimate the effect of CHX and NATA on patients’ QoL. This will be similar to that performed by Habtamu *et al*.^40^ Comparisons between the two medication groups will be adjusted for the matching variables: age and sex. The VRQoL analysis was also adjusted for socio-economic status and the HRQoL analysis adjusted for both socioeconomic status and presence of health problems during the previous 4 weeks, as these factors may confound the association between fungal keratitis and QoL. Logistic, linear and ordinal logistic regression methods will be used for binary, continuous and ordered categorical outcome variable analysis, respectively. Linear regression models and the t-test were employed to compare significant differences in QoL scores and to generate mean and mean differences between the two treatment arms in each QoL subscale and domain, respectively.
Cost-effectiveness analysis, using EQ-5D data from 3 months and direct cost data	Direct cost data will be collected at the 3 months follow-up. Economic costs to the patient can also be calculated from the EQ-5D questionnaire, which will be asked at baseline and at the 3 months follow-up. Mean direct costs incurred by patients will be compared between interventional arms using the t-test for significance. The difference from the baseline EQ-5D and the 3 months EQ-5D mean scores will also be compared in a similar fashion.
Drug adherence	The rate of drug adherence will be compared between the two treatment groups using descriptive statistics.

BSCVA, best spectacle corrected visual acuity; EQ-5D, EuroQol-5 dimensions; LMIC, low-income and middle-income countries; QoL, quality of life; TPK, therapeutic penetrating keratoplasty.

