### Outcome measures

#### Primary outcome measure

The primary outcome will be BSCVA in logMAR units at 3 months. This will be measured by a trial-certified optometrist, independent of all other aspects of the study and masked to allocation. This has been the primary outcome of several other trials and will therefore facilitate comparison. Three months is the time at which clinical experience suggests most corneal ulcers have usually healed. BSCVA is chosen as it is easy to measure and is of functional significance. We will measure the BSCVA using an LED-backlit, Tumbling-E LogMAR chart (Good-Lite, Illinois, USA) under controlled conditions. We will also measure vision using Peek Acuity, a validated smartphone application, in situations where the patient is unable to attend the hospital for follow-up and outcome data is only available through a domiciliary visit.^29^ For patients who have counting fingers (CF) vision or less, predefined logMAR values will be assigned based on previous clinical trials.^30 31^ Similarly, for patients who undergo a corneal transplant (TPK), a predefined visual acuity of 1.9 logMAR will be given, or last observation carried forward (whichever is the better vision), as per previous studies.^6^

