### Outcome assessments

Participants will be reassessed at 2 days, 1 week, 2 weeks, 3 weeks, 2 months and 3 months following enrolment. Additional examinations, outside the trial protocol schedule may be conducted by the supervising clinician as indicated. The specific assessments to be carried out at each visit are indicated in table 3. These will be conducted in the same way described for the baseline assessment as described (table 2). At each follow-up assessment, the participant will be asked about adherence to treatment and symptoms, including side effects, if still receiving trial treatment. This will be recorded in the case record file. To monitor trial medication adherence, the study participants will be asked to bring their eye-drop bottles to the 1-week, 2-week and 3-week follow-ups. The amount of remaining medication will be measured by weighing the bottle and will be compared with the anticipated remaining amount provided the drops were being used as instructed, resulting in a ratio of actually remaining to what is anticipated. Participants will be resupplied with medication as needed. The presenting visual acuity will be measured on each visit. In addition, the BSCVA will also be measured at the 3-month follow-up (primary outcome measure). At the final 3-month follow-up, the three quality of life questionnaires will be repeated. On each occasion the eyes will be examined using a slit-lamp and the cornea photographed. The IVCM will be repeated at 1, 2 and 3 weeks to determine whether there is evidence of fungal hyphae resolution with the fragmentation of linear elements. At the 1-week follow-up if the ulcer has not healed it will be rescraped for repeat culture to determine whether the keratitis is now culture positive or culture negative. We will give the study participants appointment cards for the next follow-up and they will be reminded about the follow-up a week prior to the date. Public transport costs will be paid for participants who are outpatients.

**Table 3 T3:** Baseline and follow-up assessment components

Assessment item	Baseline	Day 2	Day 7	Day 14	Day 21	Day 60	Day 90
History/baseline questionnaire	X						
Check treatment adherence		X	X	X	X	X	X
Check for side effects		X	X	X	X	X	X
Visual acuity—presenting	X	X	X	X	X	X	X
Visual acuity—BSCVA	X						X
Contrast sensitivity	X						X
Slit-lamp examination	X	X	X	X	X	X	X
Cornea photography	X	X	X	X	X	X	X
In vivo confocal microscopy	X		X	X	X		
Cornea samples (microbiology/PCR)	X		X				

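### Three-week BSCVA is a secondary outcome with its own analysis and window, but no BSCVA is scheduled between baseline and day 90

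*Protocol article*

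**What the plan says.** **Three-week BSCVA.** Table 4 (Secondary outcome analysis) makes this a secondary outcome: "We will analyse the secondary outcome of 3 weeks BSCVA in logMAR", with the method of the primary analysis. It also fixes the window: "The 3 weeks BSCVA will include values taken between 18 days and 5 weeks, with the value closest to 3 weeks used". The model it borrows is the linear regression on treatment arm and baseline BSCVA.

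**Schedule.** Under Outcome assessments, the text says that Table 3 shows which assessments belong to which visit. For acuity in general it says "The presenting visual acuity will be measured on each visit". It then adds that "the BSCVA will also be measured at the 3-month follow-up (primary outcome measure"). Table 3 has a separate row, "Visual acuity—BSCVA", marked at baseline and day 90 only.

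**Peek Acuity.** The Primary outcome measure section provides for Peek "in situations where the patient is unable to attend the hospital for follow-up" and the outcome can be obtained only by visiting the home. Table 4 lists 3-month presenting acuity by Peek, with and without pinhole, as a secondary outcome. It calls this of interest where reliable BSCVA cannot be obtained, and analyses it as the primary outcome is analysed. It then adds a sensitivity analysis for patients lost to follow-up, "by using the most recent observation of this variable".

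**The concern.** The article gives a complete visit schedule and also an outcome that the schedule does not supply. Leaving detail to a fuller protocol does not explain this, because both statements are explicit and they disagree.

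If nothing is changed, the 3-week BSCVA analysis is either empty or has to be filled with something else at the analysis stage. The obvious substitute is day-21 presenting acuity. Under a BSCVA label, and with baseline BSCVA as covariate, it would put two different measures into one model: Table 2 lists presenting, pin-hole and best-corrected acuity separately. It would also mean choosing the acuity measure after data had accrued.

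For Peek, the issue is who would have a value. If only home-visited patients do, the arms are compared in a group defined by what happened after randomisation, and the balance that randomisation gives is not guaranteed there.

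**Working it through.** No figure in the plan bears on the main point. The check sets the schedule against the outcome definitions.

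**Step 1. Three-week BSCVA**

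- Scheduled days (Table 3): 0, 2, 7, 14, 21, 60, 90.
- Window (Table 4): 18 days to 5 weeks, which is day 18 to day 5 × 7 = 35.
- Scheduled days inside the window: 21 only.
- BSCVA days (Table 3, confirmed by the visit text): 0 and 90.
- BSCVA days inside the window: none.

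Planned BSCVA values for this outcome are therefore 0 per patient. Presenting acuity is scheduled at both day 0 and day 21.

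**Step 2. Where Peek Acuity could come from**

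| Place | What it provides |
|---|---|
| Table 2 | Acuity on an ETDRS Tumbling-E chart; the only Peek tool listed measures contrast sensitivity |
| Table 3 | No Peek Acuity row at any visit |
| Primary outcome measure | Peek Acuity at home visits to patients who cannot attend |
| Table 4 | 3-month analysis by arm, plus carry-forward of the latest Peek value |

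The only collection described is at home visits, and no earlier Peek value is scheduled for the carry-forward.

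**Step 3. Possible size of the Peek comparison**

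The share of home-visited patients is not stated, so a range is assumed. Inputs: 500 randomised; SD 0.5 logMAR, which the protocol gives for 3-month BSCVA and which is assumed here to hold for Peek; equal arms. The standard error of the unadjusted difference with N patients in total is SD × √(4/N) = 0.5 × 2/√N = 1/√N.

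| Assumed share | N | Standard error (logMAR) |
|---|---|---|
| 5% | 500 × 0.05 = 25 | 1/√25 = 0.20 |
| 10% | 500 × 0.10 = 50 | 1/√50 = 0.14 |
| 15% | 500 × 0.15 = 75 | 1/√75 = 0.12 |
| 20% | 500 × 0.20 = 100 | 1/√100 = 0.10 |

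Against a margin of 0.15 logMAR, the standard error alone is 0.10 to 0.20. Adjusting for baseline BSCVA would reduce it by an amount the documents do not let one estimate.

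**The case against.** **On 3-week BSCVA.** Two replies are possible. First, the visit text allows unscheduled examinations, and some could fall in the window. But these are at the clinician's discretion and nothing says they include BSCVA; any values would come from a clinically selected few. Second, follow-up assessments are to be done as at baseline, where acuity includes BSCVA. But that describes how a measurement is made. Which measurements are made at each visit is left to Table 3, and Table 3 separates the two acuity rows. Neither reply closes the gap. It is fair to add that 3-week BSCVA appears neither in the Objectives nor among the key secondary outcomes in Table 5, so its weight is limited.

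**On Peek.** Here the other side has more. A reader might infer that Peek is collected only at home visits, that the comparison cannot be run, and that no value for carry-forward can exist. The documents do not support any of these:

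- The primary outcome section does not say that Peek is used nowhere else, and the reference in Table 4 to a most recent value hints at repeated measurement.
- The regression uses all available data, and baseline BSCVA is scheduled for everyone, so it can be fitted to whoever has a 3-month Peek value.
- Home visits are offered for missed follow-up in general, so earlier Peek values could arise. The most that can be said is that none is scheduled.
- Table 4 openly presents Peek as a fallback.

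Nor does the 15% drop-out allowance cap the Peek group at 75. Drop-outs supply no outcome, whereas home-visited patients do. The 75 in the table above is one assumed case.

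What stands is narrower. Clinic collection is not described. On the collection that is described, the comparison is small and selected after randomisation, and the carry-forward has no planned source.

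**Conclusion.** The 3-week BSCVA mismatch is a plain contradiction between Table 4 and the schedule in Table 3 and the visit text. As written, the outcome has a definition, a model and a window, but zero planned observations. This rests on the schedule alone and needs no numerical assumption. It concerns one secondary outcome, and the primary non-inferiority conclusion does not depend on it. It should be corrected because the correction is cheap and prevents a later unplanned choice of acuity measure.

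The Peek point is secondary and is a call for reconciliation. If home visits are the only source, the comparison would cover some 25 to 100 patients under an assumed 5% to 20% share, in a post-randomisation subset. If Peek is also used in clinic, the selection problem eases, but Tables 2 and 3 then need to show it. A reader might conclude that home-visit Peek values should be confined to a sensitivity analysis. The documents do not support that: the primary outcome section counts Peek at a home visit as part of measuring the primary outcome, so removing those values could add missing primary data.

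**What to change.** **Three-week outcome.** In Table 4, replace 3-week BSCVA with 3-week presenting visual acuity, keep the 18-day to 5-week window, and adjust for baseline presenting acuity instead of baseline BSCVA. Table 3 already schedules both for every patient, so the cost is a wording change. The drawback is small: presenting acuity is not best-corrected, so the result cannot be set directly beside 3-month BSCVA.

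The alternative is to keep the outcome and add BSCVA to the day-21 column of Table 3. That costs an extra refraction per patient. As Table 5 gives the trial's status as recruiting, it would yield values only for patients who had not yet passed that visit.

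**Peek Acuity.** Reconcile the Primary outcome measure section, the visit schedule and Table 4 on three things: at which visits and in whom Peek is collected; how a home-visit value enters the 3-month outcome, given that Table 4 describes Peek as presenting acuity with and without pinhole; and which earlier values, if any, the carry-forward analysis may use. If collection is limited to home visits, label the by-arm comparison as descriptive of that subset. This is wording only, unless the sponsor decides to schedule Peek for everyone.

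Both changes should be made before the allocation codes are released for analysis.

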### Sample size considerations

The study is powered to test the hypothesis that CHX is non-inferior to NATA in terms of the primary outcome (BSCVA at 3 months) at a prespecified non-inferiority margin (Delta) of 0.15 logMAR units. It is possible that CHX is non-inferior to NATA, given pilot RCT data that showed no statistically significant difference between CHX and NATA, with a Cochrane review finding a non-significant trend favouring CHX over NATA.^10 18 19^ Despite this trend favouring CHX, we have chosen to carry out a non-inferiority trial rather than a superiority trial as this is a more clinically pragmatic approach. It would be counterproductive to conduct a superiority trial and find no statistically significant difference between the two treatments leading clinicians to potentially disregard CHX as a treatment, when in fact it may be ‘non-inferior’ to NATA, and be the only available or most cost-effective treatment.

The choice of delta: This clinically meaningful difference of 0.15 logMAR was chosen as a difference of 0.15 logMAR corresponds to approximately 1.5 lines on a Snellen chart; any difference greater than this is clinically significant, as a difference of less than 0.15 log MAR could potentially be accounted for by testing/retesting error.^29^ Furthermore, it was used in the MUTT1 trial, providing methodological consistency between studies.^6^ In addition, previous studies have suggested treated ulcers improve at a mean of four Snellen lines from baseline.

Sample size was calculated for 90% power and adjusted final alpha of 0.0492, taking account of a single interim analysis using O’Brien-Fleming approach to maintain type-1 error rate of 5%. A sample size of 452 is required to detect a non-inferiority margin of 0.15-logMAR in BSCVA 3 months after enrolment between arms, assuming 0.5 SD for 3 months BSCVA and 15% drop-out. However, given approximately 10% of infections are mixed and these will be excluded from the primary analysis, 500 patients will be recruited. This sample size provides 90% power to detect superiority in BSCVA at 3 months if there is ≥0.17 LogMAR units difference as a secondary analysis.

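### The only missing-data check named for 3-month Peek presenting acuity carries the last observation forward, and the direction of its bias cannot be known in advance

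*Protocol article*

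**What the plan says.** Table 4 (Secondary outcome analysis), in the row on presenting acuity by Peek, makes the 3-month value a secondary outcome: "We will analyse the presenting VA by Peek Acuity with and without pinhole at 3 months as a secondary outcome". On the method it says: "This will be performed in the same way as the primary analysis of the primary outcome". That means linear regression on arm and baseline acuity, with missing values left out. The row then adds its one provision for patients without a 3-month value: "We will also perform a sensitivity analysis including those lost to follow-up, by using the most recent observation of this variable".

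Four other places bear on whether an earlier value can stand in for month 3:

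- Sample size considerations: "previous studies have suggested treated ulcers improve at a mean of four Snellen lines from baseline".
- The Abstract says that around a quarter of cases may progress to perforation even under intensive natamycin.
- Treatment review describes the response to antifungals as slow, with courses of 4–6 weeks usually needed.
- Outcome assessments: "The presenting visual acuity will be measured on each visit". Table 3 lists baseline and days 2, 7, 14, 21, 60 and 90.

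For missing BSCVA, the Sensitivity analyses section plans a range of imputed scenarios, models for non-random loss and, where missingness at random is judged plausible, this: "we will then apply a multiple imputation approach to the missing data".

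**The concern.** A sensitivity analysis that brings back lost patients should show how far the result depends on what happened to them. Carrying the last value forward assumes that nothing happened after the last visit. The article's own account of the disease says otherwise. Most treated eyes gain vision slowly, so a value from the first three weeks may be too poor. A sizeable minority perforate, so a value from before that event may be too good.

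The carried values also enter the regression as if measured. The interval then reflects a full sample and carries no uncertainty for the values that were filled in.

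The row says it will matter if reliable 3-month BSCVA cannot be obtained, for example because patients do not attend. It would be consulted when follow-up is poor, which is when a weak rule for lost patients does most harm.

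**Working it through.** **Inputs from the article (Sample size considerations).** Margin 0.15 logMAR, alpha 0.0492, power 90%, and "assuming 0.5 SD for 3 months BSCVA and 15% drop-out". The article equates 0.15 logMAR with about 1.5 lines, so four lines are 4 × 0.15/1.5 = 0.40 logMAR.

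**The plan's own figure first.** With 0.0492 used one-sided, n per arm = 2 × 0.5² × (1.653 + 1.282)²/0.15² = 191.3, rounded up to 192. The total is 384, and 384/0.85 = 452, as stated. That is 226 per arm before loss.

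**Assumptions, because the article does not give them.** These are the loss in each arm, the share *f* of the final arm difference already present at a lost patient's last visit, and the share *g* of an arm's own improvement that lost patients have yet to make. The 15% and the SD are planning values for BSCVA and are borrowed here for Peek acuity.

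**1. Equal loss *d* in both arms, difference emerging over time.** Estimate = true difference × [1 − *d*(1 − *f*)]. For a true difference of 0.15:

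| Loss | *f* = 0 | *f* = 0.5 | *f* = 0.9 |
|---|---|---|---|
| 15% | 0.1275 | 0.139 | 0.148 |
| 10% | 0.135 | 0.1425 | 0.1485 |
| 5% | 0.1425 | 0.146 | 0.149 |

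The largest shrinkage is 0.15 × 0.15 = 0.0225 logMAR. With no true difference, equal loss produces none, because a shortfall common to both arms cancels.

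**2. Unequal loss.** Take the natamycin improvement as 0.40 and let *T* be the true chlorhexidine deficit. Each arm's mean change becomes its own change × (1 − *d* × *g*). With *g* = 1, meaning that all improvement is missed:

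| Loss, chlorhexidine / natamycin | *T* | Chlorhexidine change | Natamycin change | Estimated difference |
|---|---|---|---|---|
| 20% / 10% | 0 | −0.40 × 0.80 = −0.32 | −0.40 × 0.90 = −0.36 | 0.04 |
| 20% / 10% | 0.15 | −0.25 × 0.80 = −0.20 | −0.36 | 0.16 |
| 10% / 20% | 0 | −0.40 × 0.90 = −0.36 | −0.40 × 0.80 = −0.32 | −0.04 |
| 10% / 20% | 0.15 | −0.25 × 0.90 = −0.225 | −0.32 | 0.095 |

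The same rule therefore turns a true 0.15 into anything from 0.095 to 0.16 in these examples, and can create a gap of 0.04 in either direction where none exists.

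**3. Precision.** If carried values have the same spread as observed ones, the standard error at 15% loss is 0.5 × √(2/226) = 0.0470, against 0.5 × √(2/192) = 0.0510 for complete cases. The interval is about 8% narrower (√0.85 = 0.92) without any new 3-month information. At 5% loss it is about 2.5% narrower (√0.95 = 0.975).

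**The case against.** The strongest reply is that the reach is small. This is one supplementary analysis of one secondary outcome, whose main analysis leaves missing values out. The primary BSCVA analysis has its own, fuller set of missing-data methods. Losses on this variable should also be fewer than 15%: the Primary outcome measure section brings in Peek "in situations where the patient is unable to attend the hospital for follow-up and outcome data is only available through a domiciliary visit", and the Lost to follow-up section plans home visits and expects low loss. All of that stands.

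Some stronger readings are tempting but not supported:

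- **Lost patients are scored at acute-phase vision.** The rule takes the latest value, which may come from day 60, and the article does not say when losses occur.
- **The rule pulls the arms together and so favours non-inferiority.** Average improvement alone does not do this. Shrinkage needs fairly balanced loss and a difference that appears after the last visit; unequal loss can widen the gap.
- **The rule conflicts with the planned multiple imputation.** That section concerns BSCVA, a different variable. Two methods for two variables do not contradict each other.
- **The trial's error rate is inflated.** With 226 per arm and one-sided 0.0492, one can calculate that the chance of declaring non-inferiority at a true 0.15 rises from 4.9% to 12.0% (*f* = 0) or 5.4% (*f* = 0.9) at 15% loss. The margin is set for BSCVA, however, and the trial's conclusion does not rest on this analysis.

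There is also an ambiguity. Table 2 measures presenting acuity on the ETDRS chart, whereas Peek is described for home visits, so it is unclear how many earlier Peek values exist to carry forward.

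**Conclusion.** The point holds as a cheap improvement to a supporting analysis. Last observation carried forward is the only missing-data sensitivity method named for 3-month Peek presenting acuity. It rests on unchanged vision, which the article's own description of the disease contradicts, and it ignores the uncertainty of the filled-in values.

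The bias is of uncertain direction. Under balanced loss and a late-emerging difference it is shrinkage, of at most 0.0225 logMAR on a true 0.15 at 15% loss and at most 0.0075 at 5%. Under unequal loss it can go the other way. These sizes depend on assumed loss rates, timing and effect shares that the article does not supply. Not knowing the direction is no defence of the rule, because a check with unknown bias cannot show that a result is robust. The primary BSCVA conclusion is untouched.

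**What to change.** In this row of Table 4, replace the last-observation rule with multiple imputation along the lines already planned for BSCVA. The imputation model should use arm, baseline acuity and the acuity recorded at attended visits, and should state which instrument supplied each earlier value.

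Add a version in which imputed chlorhexidine values are worsened in steps, for example up to 0.15 logMAR, and report where the reading of the result changes. At 15% loss in that arm, the last step moves the estimate by about 0.15 × 0.15 = 0.0225 logMAR.

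The cost is a change of wording and a little programming that can draw on the imputation planned for BSCVA. The downside is a possibly wider interval, which would reflect what is not known about the lost patients.
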